#### Randomisation

Included patients will be randomly allocated to either arm in a 1:1 ratio. The randomisation list is generated by minimisation [22] to maintain better balance than with traditional block randomisation. Stratification will be performed on gender (female/male), readmission (yes/no) and residence (at home/not at home). When a patient is considered eligible and informed consent has been obtained, randomisation will be performed automatically (on software) by an independent statistician.

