#### QOL scales

It was decided to implement two QOL questionnaires (LHFQ [20] and SF 12[21]) to assess which is more adapted to over-80 year-old HF patients. Both are well-validated and widely used. The SF12 is used on a daily basis in the geriatric department of our hospital and maybe more adapted to the elderly. A second endpoint is to assess the efficiency of this shorter QOL questionnaire, SF12, as compared to the LHFQ, in a very elderly population. They will be completed at inclusion and at 12 month for each subject. QOL scales will be sent to all participants (group A and B) at 6 months (before the 6 month visit for group B) and will be filled in by the patients without any help from medics or paramedics (to avoid bias).

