### Statistical Considerations

Due to lack of information in the literature concerning the management of over-80 year-old HF patients, it is difficult to estimate correct sample size. The number of subjects to be included is extrapolated from data obtained on younger patients, according to which 40 subjects per group will be included.

With a 2-tailed significance threshold of 0.05, statistical power of 90% and allowing for 15% loss to follow-up, 80 patients will be needed to show a difference of 20 points (σ = 25) in quality of life (LHFQ) at 6 months between the 2 randomisation arms [29]. Morcillo et al. demonstrated that a 20-point difference in LFHQ is significant and feasible in such a population at 6 months' follow-up. An interim analysis is planned. For 34 evaluable patients (17 per group), a difference in QOL score between the 2 arms will be considered significant for an adjusted α equal to 0.003 (Lan and DeMets, EaSt^© ^software). Termination for futility can thus be considered.

The number of patients included and the curve of the inclusions, the theoretical number of visits for the number of patients included, the number of visits actually made and the ratio will be presented for the 2 groups. The cumulative duration of follow-up and the "total follow-up/expected cumulative follow-up" ratio will be calculated.

All analyses will be performed on an intention-to-treat basis. Clinically relevant baseline variables and primary and secondary endpoints will be compared between groups by Chi^2 ^or Fisher-exact tests (categorical variables) and by Student's t tests or Mann-Whitney tests as appropriate (continuous variables). Multivariate analyses to control for confounding effects of variables will be performed.

The survival analysis will be conducted in univariate analysis by log-rank test to compare survival curves following Kaplan-Meier, and in multivariate analysis by the Cox proportional regression model.

To measure the evolution of parameters over time points (visits), longitudinal data analysis will be conducted by ANOVA for repeated measures followed by Tukey-Kramer post-hoc test and by random effects models to measure within-subject correlation taking account of effects over time (random intercept and slope). The impact of covariates, such as randomisation group, will be explored to assess the impact of strategies on QOL score.

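### The only test tied to the primary 6-month LHFQ endpoint is unadjusted; it is valid, but it gives up precision that baseline LHFQ and the minimisation factors could supply

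*Protocol article*

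**What the plan says.** The Objectives and endpoints section makes LHFQ at 6 months the primary criterion. Statistical Considerations then assigns one family of two-group tests to baseline variables and to primary and secondary endpoints alike. For continuous variables these are Student's "t tests or Mann-Whitney tests as appropriate (continuous variables").

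Three other statements bear on the point:

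- The Randomisation section uses minimisation and names its factors: "Stratification will be performed on gender (female/male), readmission (yes/no) and residence (at home/not at home").
- The QOL scales section says of the two questionnaires: "They will be completed at inclusion and at 12 month for each subject". A baseline LHFQ is therefore planned for every patient. The 6-month forms are sent to both groups.
- Right after the two-group tests, Statistical Considerations adds: "Multivariate analyses to control for confounding effects of variables will be performed". Its longitudinal paragraph plans repeated-measures ANOVA and random-effects models, with randomisation group as a covariate whose effect on QOL is to be explored.

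Neither of these last analyses is called primary, and neither names baseline LHFQ or the minimisation factors as covariates.

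**The concern.** A baseline measurement of the outcome is often a good predictor of its later value. A two-sample test of the 6-month scores leaves that predictable part in the error term. The same applies to the minimisation factors. Minimisation balances the arms on them, but the unadjusted standard error takes no credit for the balance and is too large if the factors predict LHFQ.

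Three things are at stake:

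- **Width of the primary interval.** The trial is a pilot meant to inform a multicentre study, so the estimate and its precision are a main product.
- **Margin against optimistic planning.** The article concedes that its sample size is extrapolated from younger patients. Extra precision would help if the true difference is below 20 points.
- **Choice among results.** An unadjusted test, an open-ended multivariate analysis and an exploratory longitudinal model all bear on the same outcome, and their order is not stated.

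**Working it through.** **Inputs from Statistical Considerations.** "With a 2-tailed significance threshold of 0.05, statistical power of 90% and allowing for 15% loss to follow-up", the article states that "80 patients will be needed to show a difference of 20 points (σ = 25) in quality of life (LHFQ) at 6 months". Hence α = 0.05 two-sided, power 90%, Δ = 20, σ = 25, loss 15%, N = 80 (40 per arm).

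**Step 1: reproduce the sample size.**

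- Normal approximation: n = 2(1.960 + 1.282)² × 25² / 20² = 32.8, so 33 per arm.
- Noncentral t: power is 89.3% at 33 per arm and 90.2% at 34, so 34 per arm are needed.
- Loss: 34 / 0.85 = 40 per arm, 80 in total.

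The stated N matches exactly, as an unadjusted t test.

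**Step 2: precision of the unadjusted test.** With 34 per arm, SE = 25 × √(2/34) = 6.06. The 95% half-width is t(0.975; 66 df) × SE = 1.997 × 6.06 = 12.1 points.

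**Step 3: adjust for baseline LHFQ.** If r is the within-arm correlation of baseline and 6-month LHFQ, the residual SD is 25√(1 − r²). The article does not give r, so 0.3 to 0.7 is an assumed range.

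| r | Residual variance cut (r²) | Residual SD | SE | 95% half-width | Power, Δ = 20 | Power, Δ = 15 |
|---|---|---|---|---|---|---|
| none | 0% | 25.0 | 6.06 | 12.1 | 90% | 68% |
| 0.3 | 9% | 23.8 | 5.78 | 11.5 | 93% | 72% |
| 0.5 | 25% | 21.7 | 5.25 | 10.5 | 96% | 80% |
| 0.7 | 49% | 17.9 | 4.33 | 8.6 | 99.5% | 93% |

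The half-widths use 66 df. An ANCOVA with arm and four covariates has 68 − 6 = 62 df, where the multiplier is 1.999 instead of 1.997. That moves a half-width by less than 0.02 points (11.55 to 11.56 at r = 0.3; 8.65 to 8.66 at r = 0.7) and power by less than 0.1 percentage point.

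In effective sample size, 34 / (1 − r²) gives about 37, 45 or 67 patients per arm at r = 0.3, 0.5 or 0.7.

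**Step 4: ignore the minimisation factors.** Suppose the factors are fully balanced and explain a share R² of LHFQ variance. In large samples the actual two-sided error rate of the unadjusted test is then 2[1 − Φ(1.96 / √(1 − R²))]. For assumed R² of 5%, 10% and 20% this gives 0.044, 0.039 and 0.028. The error is on the conservative side.

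**Step 5: chance baseline imbalance.** LHFQ is not a minimisation factor. If the baseline SD is also 25 (assumed), a one-standard-error baseline difference is 6.06 points. It carries into the 6-month difference through the regression slope, which is about r when the SDs are equal: 0.5 × 6.06 ≈ 3 points at r = 0.5.

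**The case against.** The strongest reply is that nothing is lost against plan. The 80 patients were sized for an unadjusted comparison, that comparison is valid under randomisation, and the stated power holds. A reader might infer that the trial is underpowered or its primary test invalid. Step 1 rules out the first for the article's own inputs, and Step 4 shows that any departure of the error rate is conservative. This part of the reply stands in full.

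A reader might also infer that the plan ignores adjustment altogether. It does not. Multivariate analyses are planned, and a random-effects model that includes the inclusion visit would use baseline LHFQ. Covariate lists are commonly left to a full protocol or SAP, so their absence from an article is no fault. What remains is narrower: the one test expressly attached to the primary endpoint is unadjusted, and the adjusted analyses are not designated to replace it.

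Two further inferences go beyond the text:

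- **Dilution.** One might say that the longitudinal model dilutes the month-6 effect by averaging over visits. The article does not specify a group main effect averaged over visits. It speaks of models that take account of effects over time.
- **Full carry-over of imbalance.** One might say that a baseline imbalance passes whole into the primary estimate. It passes only in proportion to the slope (Step 5), and the ordinary confidence interval already covers that chance variation.

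Finally, r may be low. Baseline is taken at discharge from an acute episode, while the 6-month form is mailed and completed without help from staff. At r = 0.3 the gain is only from 90% to 93% power. This is fair, and it is why a range is given. Likewise, no figure in the article shows that gender, readmission or residence predict LHFQ.

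**Conclusion.** The point holds as one of efficiency, not validity. The named primary comparison uses neither baseline LHFQ nor the minimisation factors, and a better method is available from data already being collected.

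The size of the gain depends on a correlation that the article does not give. Over the assumed range of 0.3 to 0.7, the half-width would fall from 12.1 to between 11.5 and 8.6 points, and power for a 20-point difference would rise from 90% to between 93% and 99.5%. The gain is slight at the low end and substantial at the high end. These figures assume 34 evaluable patients per arm, an SD of 25 in both arms and a linear relation between baseline and 6-month scores. They credit nothing to the minimisation factors.

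The wording of the plan is clear enough to be confident about what the primary test is. The amount of precision given up is not known. For a single-centre pilot this is a worthwhile improvement, not a defect that endangers the trial.

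**What to change.** Name one primary analysis in advance: an ANCOVA of 6-month LHFQ on arm, baseline LHFQ, gender, readmission and residence, reporting the adjusted mean difference with its 95% confidence interval. Keep the unadjusted t or Mann-Whitney test as supportive, and state that the multivariate and random-effects analyses are secondary.

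The cost is a change of wording and four degrees of freedom (66 to 62 with 68 evaluable patients). No new data, visits or patients are needed, and the sample size of 80 can stand.

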**Figure 2 F2:**
[figure not shown]
**Flow chart describing HF 80 study investigational procedure**. CE: clinical examination; EKG: electrocardiogram; MMSE: mini mental state examination; QOL: quality of life scale; 6MWT: 6 minutes walking test; Seattle HF: Seattle heart failure score; TTE: transthoracic echocardiography.

• Clinical examination: NYHA class; weight; height; heart rate; blood pressure; right, left or both HF symptoms; triggering factor; cardiovascular risk factors; thyroid pathologies; personal cardiovascular history;

• Quality of life questionnaires (LHFQ [20], SF 12 [21]);

• Six-minutes walking test (6MWT);

• Electrocardiogram (EKG);

• Transthoracic echocardiography (TTE);

• Blood test (haemoglobin, kaliaemia, natraemia, liver assessment, bilirubin, Modification in Diet Renal Disease (MDRD) [23], N-Terminal of pro-Brain Natriuretic Peptide (NT-pro-BNP), and nutritional tests (C-reactive protein, albumin, prealbumin and orosomucoid);

• Renin, aldosterone and collagen peptides [type 1 collagen telopeptide (ICTP), aminoterminal propeptide of type I procollagen (PINP), aminoterminal propeptide of type III procollagen (PIIINP)], and galectin 3;

• Mini mental state examination (MMSE) [24].

During primary hospital care for acute HF and at discharge, both groups will have the same management with initiation of the same treatments, following guidelines [11,12].

Group A subjects will be followed up by their usual GP and cardiologist without any day-hospital care ("usual care" management). The GP and cardiologist will manage treatment optimisation as they are used to doing.

Group B subjects will have the same management as group A but will also receive day-hospital care. The first 3 visits will be at 3 weekly intervals, except in case of unstable HF, and then every 6 weeks for 12 months, to optimise treatment.

During each day-hospital visit in group B, certain data will be recorded to optimise HF management:

• Clinical examination (NYHA class, HF symptoms, blood pressure, heart rate);

• Blood sample (kaliaemia, MDRD [23], NT-pro-BNP);

• Electrocardiogram;

• Optimised treatment doses, if possible, for ACEi, beta-blockers, angiotensin receptor blocker and mineralocorticoid receptor antagonist.

All the visits and contents are described in Table 3.

**Table 3 T3:** Schedule of visits and contents

	Group A		Group B					

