Treatment compliance will be analysed initially in a descriptive step and, if necessary, included in multivariate analysis.

A 2-tailed p value of 0.05 will be considered statistically significant (except in interim analysis). All analyses will be performed by STATAv11 (StataCorp, College Station, Texas, USA).

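### Treatment compliance, measured after randomisation, may enter the multivariate models; in any model read as the effect of arm, the arm coefficient would then no longer be the intention-to-treat effect

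*Protocol article*

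**What the plan says.** All of the analysis text is under Statistical Considerations in the protocol article.

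- Compliance: "Treatment compliance will be analysed initially in a descriptive step and, if necessary, included in multivariate analysis". No criterion is given for when inclusion is necessary.
- Analysis principle: "All analyses will be performed on an intention-to-treat basis".
- Between-group comparison of baseline variables and of primary and secondary endpoints: for continuous variables, "by Student's t tests or Mann-Whitney tests as appropriate (continuous variables"). This comparison has no covariates.
- Multivariate models: "Multivariate analyses to control for confounding effects of variables will be performed". A Cox model is planned for survival.
- Longitudinal models: "The impact of covariates, such as randomisation group, will be explored to assess the impact of strategies on QOL score".

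Investigation Procedure describes the intervention. Both groups start the same treatments in hospital. After discharge only group B has day-hospital visits, three at 3-week intervals "and then every 6 weeks for 12 months, to optimise treatment". Their content includes "Optimised treatment doses, if possible, for ACEi, beta-blockers, angiotensin receptor blocker and mineralocorticoid receptor antagonist".

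**The concern.** The multivariate analyses are there to control confounding. A variable that arises after allocation, and may be shifted by it, does not confound the comparison of arms. The strategy under test works largely through the heart failure drugs that patients take and the doses they reach, so compliance plausibly lies on the path from arm to quality of life.

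Holding compliance fixed has two consequences. It takes out of the arm coefficient whatever part of the effect passes through compliance. It also makes the arms non-comparable on anything, measured or not, that affects both compliance and quality of life.

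The trigger adds to the problem. Inclusion is decided after a look at the compliance data, with no stated rule. A natural prompt would be a difference between arms, which is the situation in which adjustment does harm.

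The article says that this pilot prepares a national multicentre study, so a distorted estimate could carry forward into that trial's design.

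**Working it through.** **Inputs from the document** (Statistical Considerations): two-sided α 0.05, power 90%, difference 20 points, SD 25, 15% loss, N = 80. Allocation is 1:1 (Randomisation).

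**The plan's own figure.** n per arm = 2(1.960 + 1.282)² × 25² / 20² = 32.8, so 33. Dividing by 0.85 gives 39 per arm, 78 in total. The t-distribution version gives 33.8, so 34; 34/0.85 = 40 per arm, 80 in total. N = 80 reproduces. With 34 evaluable per arm and no covariate, power is 0.90 (t test).

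**Assumed inputs.** The document gives no link between compliance and outcome. Let *s* be the share of the 20 points that runs through compliance, and *d* the between-arm difference in compliance in within-arm SDs. The within-arm SD of LHFQ stays at 25. Benefit is counted as positive.

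**Formulae for the adjusted model.**
- Arm coefficient = 20(1 − s).
- Slope of outcome on compliance: b = 20s/d.
- Residual SD = √(625 − b²).
- SE of the arm coefficient ≈ residual SD × √(2/34) × √(1 + d²/4). The last factor is the loss of precision from the correlation of arm with compliance.

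**Example, s = 0.5 and d = 1.** b = 10; residual SD = √525 = 22.9; SE ≈ 22.9 × 0.2425 × 1.118 = 6.21; coefficient 10; ratio 1.61.

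**Example, s = 0.5 and d = 0.5.** b = 20; residual SD = √225 = 15; SE ≈ 15 × 0.2425 × 1.031 = 3.75; coefficient 10; ratio 2.67. Power is higher than at d = 1 because compliance now explains much of the outcome variance and is less correlated with arm. The estimate is just as far from 20.

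**Simulation** (least squares, 34 per arm, 3000 runs per row):

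| d (SD) | s | Adjusted arm coefficient | Power |
|---|---|---|---|
| 0 | 0 | 20.0 | 0.90 |
| 0.5 | 25% | 14.9 | 0.72 |
| 0.5 | 50% | 10.0 | 0.73 |
| 1 | 0 | 20.0 | 0.82 |
| 1 | 25% | 15.0 | 0.60 |
| 1 | 50% | 10.1 | 0.35 |
| 1 | 75% | 5.0 | 0.15 |

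The row d = 0.5 with s = 75% cannot occur: b would be 30, more than the SD of 25. With d = 1 and s = 0 the coefficient is unbiased, but precision is lost.

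**Bias from a common cause.** Assume no true effect, d = 1, and an unmeasured factor that correlates 0.5 with compliance and moves the outcome by 10 points per SD. The expected bias is −10 × 0.5 × 1 = −5 points. The simulation gave −4.9 points and a type I error of 0.10 in place of 0.05.

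**The case against.** The strongest reply is that the main comparison never contains compliance. The endpoints, including 6-month LHFQ, are compared by t or Mann-Whitney tests, and the sample size is the one for a plain comparison of two means. This stands. A reader might infer that the primary result is compromised, or that an effective strategy would be reported as ineffective. The document does not support that: it would need the adjusted model to displace the unadjusted comparison, and nothing in the article says that it does. The article does not label either analysis as primary.

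Second, that the intervention changes compliance is an inference from its design. The article describes extra visits and dose optimisation and says nothing about adherence. This also stands, and if compliance is equal between arms the coefficient does not move.

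Third, a reader might conclude that the whole effect would be adjusted away. Only the mediated share is removed, so that is true only under full mediation.

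Fourth, adding a covariate excludes and reassigns nobody, so there is no flat contradiction with intention-to-treat in the sense of who is analysed and in which arm. That is right. The conflict is about what is estimated: a coefficient conditional on compliance is not the effect of being allocated to the strategy.

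Fifth, the compliance model might be meant as purely explanatory, and a condensed article may leave its definition to a fuller plan. The definition of compliance can be left there. But the sentence itself is a stated rule, and the same section uses modelling to judge how the strategies affect quality of life, so the permission reaches models that carry the treatment comparison.

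**Conclusion.** The point holds for the multivariate, Cox and longitudinal models wherever the arm term is read as the effect of the strategy. It does not reach the unadjusted comparison of 6-month LHFQ.

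The direction of the mediation loss is clear if compliance differs between arms and affects quality of life in the intended way. The size is not known from the document. Every coefficient and power figure above rests on assumed values for the mediated share and the between-arm compliance difference. The power figure is especially sensitive: at a 50% share it moves from about 0.35 to about 0.73 when the assumed difference goes from 1 SD to 0.5 SD. The coefficient of about 10 points is the same in both cases.

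This is worth changing because the sentence sets a rule with an open, data-dependent trigger, and the repair is almost free.

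**What to change.** Replace the compliance sentence in Statistical Considerations with:

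> Treatment compliance and doses reached will be described by arm and will not be covariates in any model estimating the effect of randomised group; covariates in those models are limited to baseline variables, including the minimisation factors. Any analysis involving compliance will be separate, labelled exploratory and not intention-to-treat.

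The minimisation factors are gender, readmission and residence (Randomisation).

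Randomisation should not be proposed as an instrument for compliance. That would require arm to act on quality of life only through compliance, whereas group B also has extra visits, examinations, blood tests and dose changes that may act by other routes. The Discussion itself names the extra visits as a potential bias.

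The cost is a short replacement text. N = 80 is unchanged, no data collection changes, and compliance is still reported.

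### The final primary test is left at 0.05 although alpha is spent at an interim efficacy look, so overall two-sided error is 5.1%, not 5%

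*Protocol article*

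**What the plan says.** All the relevant statements are in the Statistical Considerations section of the protocol article.

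- **Design error rate and power:** "With a 2-tailed significance threshold of 0.05, statistical power of 90% and allowing for 15% loss to follow-up".
- **Sample size:** "80 patients will be needed to show a difference of 20 points (σ = 25) in quality of life (LHFQ) at 6 months". The Randomisation section gives 1:1 allocation.
- **Interim:** at 34 evaluable patients, 17 per group, a difference in the quality-of-life score "will be considered significant for an adjusted α equal to 0.003". The method is named as Lan and DeMets, computed in EaSt. The text adds that stopping for futility may be considered, but gives no futility boundary.
- **Level for every other analysis:** "A 2-tailed p value of 0.05 will be considered statistically significant (except in interim analysis".

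The article gives no reduced level for the final analysis of the primary endpoint.

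**The concern.** The interim rule lets the trial claim a difference on the primary endpoint at half information. That is a chance to reject the null hypothesis, and it uses alpha. A Lan-DeMets plan divides one total error rate between the looks, so a non-zero interim level means a final level below 0.05. The section uses the first half of that plan (0.003) and then states a final threshold as though nothing had been spent.

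At stake is whether the trial holds the two-sided 5% on which it was sized. There is also a practical risk. If the final p value landed just below 0.05, the closing sentence of the section would call it significant and the spending plan would not. That dispute should be settled before the data are seen.

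**Working it through.** **Inputs.** From Statistical Considerations: two-sided alpha 0.05, power 90%, difference 20 points, SD 25, loss to follow-up 15%, total 80, interim at 34 evaluable patients, interim level 0.003, final level 0.05. From Randomisation: 1:1 allocation.

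**Step 1: reproduce the sample size.** The standardised difference is 20/25 = 0.8.

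- Normal approximation: n = 2(1.960 + 1.282)² × 25²/20² = 32.8, so 33 per arm; 33/0.85 = 38.8, so 39 per arm and 78 in total.
- t test: 33 per arm gives 89.26% power and 34 per arm gives 90.15%, so 34 are needed; 34/0.85 = 40 per arm and 80 in total. This matches the protocol exactly.

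The plan therefore implies 80 × 0.85 = 68 evaluable patients.

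**Step 2: reproduce the interim level.** The information fraction is t = 34/68 = 0.5. The protocol does not name the spending function. With O'Brien-Fleming-type spending on each side at 0.025:

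α(t) = 4[1 − Φ(2.2414/√t)] = 4[1 − Φ(3.170)] = 0.00305.

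This matches the stated 0.003 and supports both the spending shape and the 68 evaluable patients.

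**Step 3: overall error as written.** Under the null hypothesis the interim and final statistics are bivariate normal with correlation √0.5 = 0.707. The cut-offs are |Z₁| > 2.968 (level 0.003) and |Z₂| > 1.960 (level 0.05).

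Overall error = 1 − P(|Z₁| ≤ 2.968 and |Z₂| ≤ 1.960) = 0.0510.

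This is less than the simple sum of 0.053 because most null trials that cross at the interim would also cross at the end. A simulation of t tests at 17 and 34 per arm (4 million replicates) gave 0.0510, standard error 0.0001.

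**Step 4: the final level that restores 0.05.** Holding the interim at 0.003 and solving for the final level:

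| Information fraction at interim | Overall error with final 0.05 | Final level needed |
|---|---|---|
| 34/80 = 0.425 | 0.0513 | 0.0487 |
| 34/68 = 0.500 | 0.0510 | 0.0490 (z = 1.968) |
| 34/66 = 0.515 | 0.0509 | 0.0491 |

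**Step 5: effect on power.** With 34 evaluable per arm, a single-look t test has 90.15% power at 0.05 and 89.99% at 0.049, a loss of 0.16 points. Counting both looks (normal approximation, non-centrality 0.8 × √(34/2) = 3.298), power goes from 91.0% to 90.9%.

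**The case against.** The strongest reply is that the sentence with 0.05 is a general convention closing the statistics section. It covers baseline, secondary, survival and longitudinal analyses, for which 0.05 is appropriate, and it names neither the primary endpoint nor a final analysis. On that view 0.05 is the overall level, and the final boundary follows from the named method and would sit in the full protocol or SAP. The reply adds that this is a single-centre pilot, that the excess is 0.1 percentage point, that 0.0490 depends on an unstated spending function and an inferred 68 evaluable patients, and that the only early stopping mentioned is for futility.

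Part of this stands. The effect is very small, and the exact final level depends on the actual information fraction.

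The rest does not remove the point. The article does more than leave the final level to another document: it states a threshold and exempts only the interim, so a reader who follows it tests the final primary endpoint at 0.05. The interim wording permits a claim of significance, which spends alpha whether or not the trial then stops. A futility option with no boundary, which need not be used, cannot be credited with recovering any of it. Calling the trial a pilot does not change the two-sided 5% it set for itself.

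**Conclusion.** The point holds. The stated final threshold is inconsistent with the alpha-spending method chosen in the same section. The overall two-sided type I error is 0.0510 instead of 0.05 (0.0509 to 0.0513 over the fractions examined), and the consistent final level is 0.0490 (0.0487 to 0.0491).

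This rests on a literal reading of the closing sentence, on a non-binding futility option and, for the central figures, on 68 evaluable patients. It is an error in a stated decision rule with a small numerical effect; it does not undermine the sample size.

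**What to change.** Replace the general sentence on significance with one that separates the final primary test from the rest, for example: *The final analysis of the 6-month LHFQ score will be tested at a two-sided level of 0.049, recomputed from the spending function at the information fraction actually reached at the interim; other endpoints will be tested at a nominal two-sided 0.05.*

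Name the spending function in the same place (the figures fit the O'Brien-Fleming type). Also clarify the futility remark, which does not follow from an efficacy level of 0.003. If no claim of efficacy is intended at the interim, say so and delete the 0.003; the final test can then stay at 0.05.

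The cost is a sentence or two of text, no extra patients, and less than 0.2 percentage points of power.
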